## Abstract

**Background:**

Community service providers (CSPs) play an integral role in the health care of low-income Hispanic or Latinx (HL) communities. CSPs have high-stress frontline jobs and share the high-risk demographics of their communities. Relational savoring (RS) has been associated with lower cardiovascular reactivity and psychosocial benefits, with particular promise among HL participants. In this study, we aim to identify RS’s potential in promoting CSPs’ cardiometabolic health and, in so doing, having broader impacts on the community they serve.

**Objective:**

This randomized controlled waitlist study aims to examine the effect of an RS intervention on (1) CSPs’ cardiometabolic health (cardiometabolic risk factors and outcomes) and (2) CSPs’ threats to leaving the workforce.

**Methods:**

We will recruit a sample of 80 CSPs from community health agencies serving low-income HL populations. Participating CSPs will be randomized into an experimental or a waitlist control. Participants will complete 1 or 2 baseline assessment batteries (before the intervention), depending on the assigned group, and then complete 2 more assessment batteries following the 4-week RS intervention (after the intervention and at a 3-mo follow-up). The RS intervention consists of guided reflections on positive moments of connection with others. Electrocardiogram data will be obtained from a wearable device (Polar Verity Sense or Movisens) to measure heart rate variability. The primary outcome is cardiometabolic health, consisting of cardiometabolic risk (obtained from heart rate variability) and cardiometabolic health behaviors. The secondary outcomes include CSPs’ threats to leaving the workforce (assessed via psychological well-being), intervention acceptability, and CSPs’ delivery of cardiometabolic health programming to the community (exploratory). Analyses of covariance will be used to examine the effects of RS on cardiometabolic health and on CSPs’ threats to leaving the workforce, comparing outcomes at baseline, postintervention, and at follow-up across participants in the experimental versus waitlist group.

**Results:**

The study has been approved by the University of California, Irvine, Institutional Review Board and is currently in the data collection phase. By May 2023, 37 HL CSPs have been recruited: 34 have completed the baseline assessment, 28 have completed the 4 intervention sessions, 27 have completed the posttreatment assessment, and 10 have completed all assessments (including the 3-mo follow-up).

**Conclusions:**

This study will provide valuable information on the potential of RS to support cardiometabolic health in HL CSPs and, indirectly, in the communities they serve.

**Trial Registration:**

ClinicalTrials.gov NCT05560893; https://clinicaltrials.gov/study/NCT05560893

**International Registered Report Identifier (IRRID):**

DERR1-10.2196/51427

## Introduction

### Background

Ethnic and racial disparities in cardiometabolic health within the United States have been widely documented [1-5]. Racial-ethnic minoritized and historically underrepresented groups, including Hispanic or Latinx (HL) Americans, face higher cardiometabolic risks, such as obesity, diabetes, hypertension, and dyslipidemia, than non-HL White Americans [6,7]. According to data obtained from the National Health Interview Survey of 2018, HL adults are 1.3 times more likely to die from diabetes and 70% more likely to be diagnosed with diabetes by a physician than non-Hispanic White (NHW) adults [8]. Similarly, HL Americans are 1.2 times more likely to be obese than NHW Americans, whereas HL women are 20% more likely to be overweight than their NHW counterparts [9]. The etiology of cardiometabolic risk disparities in racial-ethnic minoritized communities, including low-income HL communities, is multifactorial and includes socioeconomic, behavioral, and environmental factors. Cultural and language barriers, lack of health care access, and differences in education and employment opportunities contribute to these disparities [1,5,10]. Community service providers (CSPs), also called *promotores de salud*, are members of the community who provide culturally appropriate health education and information, offer support and care, and advocate for the community’s health needs [11]. These roles empower HL CSPs to help community members overcome or withstand the barriers that contribute to health inequalities.

Through culturally accessible programming, CSPs help prevent and manage chronic diseases, including cardiometabolic diseases, in the communities they serve. Indeed, CSPs play a significant role in reducing health risks and disease burden as well as in the management of various health problems, including hypertension, diabetes, HIV infection, cancer, and cardiovascular disease [12-16]. Community interventions led by CSPs have been proven to effectively lower cardiometabolic risk factors in HL communities while being affordable and well received by community members [12-16]. These include, among others, prevention programs targeting diabetes and obesity, which effectively impact risk factors such as blood pressure, low-density lipoprotein cholesterol, triglycerides, insulin, sedentary behaviors, and one’s weight [12-16]. There are many advantages to CSPs belonging to the same communities they serve, including cultural and linguistic understanding, trust, credibility, and rapport. All of this contributes to community members’ engagement and retention in interventions that improve health outcomes and provide long-term support. However, sharing the same demographic characteristics also means that HL CSPs face the same high cardiometabolic risks as the community members they serve. In fact, it is often the case that CSPs are individuals who themselves have experienced health challenges and have learned to manage their conditions (eg, diabetes, HIV). In addition to providing support to others, as they have been trained to, their own health concerns might still require monitoring and self-management. Furthermore, the high-stress nature of their occupations may further amplify health risks. This is especially true when considering the extensive stress that the COVID-19 pandemic brought to frontline health care workers, including CSPs. In support of this assertion, a qualitative analysis found that the pandemic affected CSPs’ work and daily life, leading to psychological and social stress [17].

CSPs, along with all frontline health care professionals (HCPs) during the pandemic, experienced acute psychological distress and associated effects [17]. A study analyzing the role of CSPs in the COVID-19 pandemic response reports that CSPs faced significant exposure to stress and grief, among other difficulties [18]. In addition, HL communities, as well as other minoritized communities, were more likely to be exposed to the SARS-CoV-2 virus, to experience severe forms of COVID-19, and to face higher mortality rates [19,20]. Understandably, this led to catastrophic financial and social consequences in low-income HL communities. Owing to the comprehensive support that CSPs provide to community members, which addresses not only physical health but also various financial and social needs (eg, unemployment, housing insecurity, food insecurity, domestic violence, and language barriers to navigate legal paperwork), CSPs carried a significant burden [17]. Considering the fact that they are at higher risk for negative health outcomes (eg, diabetes, high blood pressure, and overweight) based on demographics alone and the role they played during the pandemic, which led to heavy workloads and high stress, CSPs may face substantial risk for cardiometabolic disease. Nevertheless, to the best of our knowledge, there have been no interventions aimed at protecting cardiometabolic health specifically in CSPs.

By placing enormous demands on CSPs, the aftereffects of COVID-19 have placed CSPs at risk of professional burnout, endangering their abilities to deliver this care [17,21]. CSPs play a crucial role in the health of underserved communities, but to carry out their greatly needed service, there must be a system that promotes and protects their health and well-being. Supporting CSPs is a matter of equity; in response to the health care system failure to adequately support medically underserved communities, the CSP model represents these communities’ efforts to promote health and build resilience. Although no previous studies have specifically examined how CSPs’ physical and psychological well-being relates to the quality and reach of their services, researchers have investigated how burnout in other HCPs affects the quality and safety of the care they provide [22,23]. In line with theory, a meta-analysis comprising 210,669 HCPs concluded that burnout (depersonalization, emotional exhaustion, and reduced personal accomplishment) is negatively associated with quality (perceived quality and patient satisfaction) and safety of care [22]. Similarly, in a systematic literature review, burnout among physicians was associated with decreased productivity, as evidenced by the number of sick days, hours worked, number of patients seen, and intent to leave the profession [23]. Considering these relationships between HCPs’ burnout and reduced productivity, impaired quality of care, and reduced safety of the care provided, it is reasonable to expect similar associations between CSPs’ well-being and the reach and quality of the services delivered to the community. As such, interventions designed to promote CSPs’ well-being and prevent their burnout are a necessity.

### Relational Savoring: A Culturally Congruent Approach

Relational savoring (RS), based on positive psychology and attachment theory, is a brief intervention in which one deeply reflects on a positive emotional experience involving a moment of connection with another person [24]. The underlying premise is that focusing on a memory of positive connection will augment the meaning and positive emotion associated with this interpersonal experience [24]. Through this process, one’s sense of psychological agency, fulfillment, and satisfaction are enhanced [24]. Similarly, per attachment theory, experiences of felt security such as *safe haven* (a time when an attachment figure provided care of comfort) and *secure base* (a time when the support provided by an attachment figure allows one to take a risk one would not have taken otherwise) in our early relationships constitute the basis of later socioemotional health [25]. As such, moments of closeness recalled in an RS intervention include times when one supported (secure base) or comforted (safe haven) another person and felt deep positive emotions such as joy, peace, satisfaction, or love [24]. For CSPs, experiencing interpersonal connectedness when helping members of their community is a common occurrence [26], thereby underscoring the cultural congruence of this intervention. RS has the potential to prolong and enhance the attention given to these moments, helping CSPs lower stress and motivating them to continue engaging in their meaningful and necessary work.

Although RS has not previously been tested with CSPs or HCPs, other interventions rooted in positive psychology, such as the Web-based Implementation for the Science of Enhancing Resilience (WISER) intervention, have been found to decrease burnout and depression and support work-life integration in neonatal intensive care unit HCPs [27]. The WISER intervention includes 6 modules, 2 of which are titled “Three Good Things” and “Relationship Resilience” and refer to reflecting on 3 positive moments that occurred that day and reflecting on positive interactions, respectively. Considering RS’s focus on reflecting and enhancing positive emotions linked to a relational memory, there are considerable similarities with these 2 modules of WISER. Likewise, support for the RS intervention exists in its prior findings with other samples. Findings across studies with parent-child dyads, long-distance couples, older adults, and male adolescents in residential treatment have shown that RS can improve emotional states, psychological agency, relational schemas, and relationship satisfaction compared with control conditions [28-32]. Likewise, the RS intervention shows promise in affecting physical health by impacting health behaviors and lowering heart rate [29,31]. In addition, previous studies report that RS might be especially effective in HL populations because of its compatibility with cultural values [28]. Considering the potential of RS in positively impacting psychological and physical health in different populations, as well as evidence suggesting cultural computability, it is worth exploring its effect among HL CSPs.

In this study as well as in previous studies [26,28-32], while maintaining its core characteristics, the RS intervention is tailored to our priority population of HL-serving CSPs. This was done based on discussions held between the investigative team and the CSPs regarding what brings them meaning in relation to the job. Furthermore, the results of a qualitative study of *promotores’* experiences during the pandemic revealed important insights regarding the meaning derived from work as well as the unique challenges posed by working during the pandemic [17]. The challenges reported included enduring their own and their community’s losses, which placed them at risk of compassion fatigue or vicarious traumatization, along with feelings of grief and anxiety [17]. However, by being able to provide help to the community during difficult times, their work also provided a source of agency and meaning [17]. Therefore, in this investigation, RS focuses on assisting CSPs’ recall moments of connection with community members while doing their work and engaging with the community.

Finally, the participants in this study are all CSPs who serve the HL community, with most of them being HL themselves. Although we recognize that *Hispanic* and *Latinx* refers to individuals with origins in different countries, racial backgrounds, and levels of acculturation, there are cultural values that seem to be shared across communities of Latin American origin. Shared values include, among others, *simpatía*, the inclination toward emotional positivity or warmth and the avoidance of negativity or conflict with others, and *familismo,* valuing close family connections above the individual or self [33,34]. Considering that RS focuses on finding and reflecting on moments of warmth and connection, this intervention is culturally compatible with HL populations without the need for substantial tailoring [24]. In agreement, a previous study reported that HL mothers, but not non-HL mothers, showed a greater response to an RS intervention than to a personal savoring intervention [24]. Likewise, besides cultural congruence, HL CSPs share the fact that their job is caring for and supporting community members. In other words, CSPs’ day-to-day interactions with members of their communities may lead to various moments of connection that can be used throughout the RS intervention [26]. As such, the characteristics of their job may facilitate engagement with RS.

CSPs are required to support low-income HL communities’ health. If their physical and psychological well-being are at risk, their ability to reach community members through their programming is compromised. Considering the challenges endured in the pandemic and the risk factors associated with both their demographic characteristics and their job responsibilities, there is a need for interventions that support HL CSPs’ well-being. Bearing in mind this intervention’s compatibility with CSPs’ occupation and cultural background, RS holds immense potential.

### Objectives

This study aims to analyze the effects of an RS intervention on (1) HL CSPs’ cardiometabolic health (cardiometabolic risk and health behaviors) and (2) the risks of CSPs leaving the workforce. We hypothesize that compared with participants assigned to the waitlist control condition, those in the RS condition will exhibit the following health improvements:

1a. Exhibit lower cardiometabolic risk (lower heart rate variability [HRV]) during a discrimination stressor task1b. Report more favorable cardiometabolic health behaviors pertaining to sleep, exercise, and diet2a. Show reduced threats to CSPs leaving the workforce (greater work satisfaction and psychological agency and lower burnout)2b. Exploratory hypothesis: That introduction of the RS intervention into agencies will result in greater engagement, as evidenced by the following: agencies will show increases in their demonstrated reach to community members through their health programing (ie, fewer absent days, more health-related events offered, larger community attendance at their events, and larger retention of community members in their programs) during the period following the introduction of RS as compared with the 6 months preceding the introduction of RS

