### Measures

#### Primary Outcomes

All the constructs and measures assessed are summarized in Table 1.

All assessments are available in both English and Spanish. Cardiometabolic health, as indicated by cardiometabolic risk and cardiometabolic health behaviors, will be the primary outcome and will be measured before the intervention, after the intervention, and at the 3-month follow-up. Cardiometabolic risk will be measured via HRV in response to a stressor task. The stressor task will consist of a discrimination stream-of-consciousness (SOC) task [35,36], where participants will talk for 4 minutes about an occasion where they felt discriminated against. Before completing the SOC task, participants will complete a questionnaire [36] that will provide them with a list of commonly occurring discrimination events from which they can select an event that has occurred to them. Vagally mediated HRV will be calculated from the variability of the interbeat intervals obtained from electrocardiogram (ECG) data. ECG data will be recorded using a Polar Verity Sense heart rate monitor or Movisens device, small wearable devices that the participants will place in their arm or chest, respectively, during the stressor task and at rest (before and after the stressor task baseline measures). Favorable cardiometabolic health behaviors include behaviors pertaining to sleep, exercise, and diet and will be assessed using the Pittsburgh Sleep Quality Index [37], the International Physical Activity Questionnaire–Short Form [38], the Food Behavior Checklist [39], the 36-Item Short Form Health Survey [40], and 2 self-developed scales (subjective assessment of overall health and impairment owing to overall health).

The measures and tasks used to assess the primary outcome, cardiometabolic health, are described in the following sentences:

1. Everyday Discrimination Scale: the participants will complete a Spanish version of the Everyday Discrimination Scale [36], a 9-item scale that assesses the frequency and the attribution of discrimination experiences (eg, In your day-to-day life, how often are you treated with less respect than other people are?) to assist them in identifying a discrimination experience to speak about in the SOC task. Items are rated on a scale of 0 (never) to 5 (almost every day), with higher scores indicating a higher frequency of discrimination experience. Previous studies have demonstrated good reliability and validity in HL samples [41].

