**Primary outcome: cardiometabolic health**			
	**Cardiometabolic risk**		
		Stressor-level heart rate variability	Everyday Discrimination Scale SOC^a^ task

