## Discussion

### Expected Findings

This study will provide valuable information on the potential of RS to positively impact cardiometabolic health in HL CSPs and, indirectly, in the communities they serve. By improving cardiometabolic health behavior and lowering HRV, RS can reduce the risk of cardiovascular disease in CSPs. Simultaneously, supporting CSPs’ well-being and engagement can improve the community’s cardiometabolic health. Theoretically, if CSPs are healthy both psychologically and physically, their risk of leaving the workforce is reduced, and more community members will be reached and impacted by CSPs’ cardiometabolic health programming. This is particularly important in the context of communities’ recovery following the COVID-19 pandemic and considering the unique ability of CSPs to reach community members in ways that the health care system is unable to do. Therefore, RS interventions aimed at CSPs have the potential to influence well-being and cardiometabolic health at both individual and community levels.

Importantly, RS appears to be compatible with both HL CSPs’ cultural background and the characteristics of their job. This is evidenced by previous studies reporting greater benefits of RS in HL (vs non-HL) participants [28]. Likewise, CSPs are in constant interaction with community members, mostly in the context of CSPs providing some sort of support (eg, information, resources, and socioemotional support) [17,26]. This may facilitate engagement with the memories preferred for the RS intervention: moments where the participant helped or comforted others (safe haven) or when the participant provided support or encouragement (secure base) [24]. Congruence with both culture and occupation makes RS a particularly promising approach to support this population, especially when considering additional factors pertaining to the delivery of the intervention.

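### Hypothesis 1a and the Expected Findings state the direction of benefit for vagally mediated HRV backwards, which reverses how the signed effect size would be read

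*Protocol article*

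**What the plan says.** Under Objectives, the article introduces its list of expected effects by saying that, compared with waitlist, "those in the RS condition will exhibit the following health improvements". The first item, 1a, is "Exhibit lower cardiometabolic risk (lower heart rate variability [HRV]) during a discrimination stressor task". The Discussion (Expected Findings) puts the same direction in causal form: "By improving cardiometabolic health behavior and lowering HRV, RS can reduce the risk of cardiovascular disease in CSPs".

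Methods, Primary Outcomes, gives HRV its role: "Cardiometabolic risk will be measured via HRV in response to a stressor task". It also names the index: "Vagally mediated HRV will be calculated from the variability of the interbeat intervals obtained from electrocardiogram (ECG) data". Table 1 gives the construct as "Stressor-level heart rate variability".

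The rationale appears elsewhere. The Abstract (Background) says: "Relational savoring (RS) has been associated with lower cardiovascular reactivity and psychosocial benefits". The Introduction section on relational savoring says the intervention shows promise for physical health by "impacting health behaviors and lowering heart rate".

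The Data Analytic Plan specifies analyses of covariance with baseline HRV as a covariate. It states no sidedness and no sign convention, and it says the aim is effect sizes for future studies rather than statistical significance.

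**The concern.** HRV is the sole measure of the cardiometabolic-risk component of the primary outcome and the only physiological measure in it. A vagally mediated index is higher when vagal activity is higher. Vagal activity slows the heart, and stress withdraws it. An intervention that dampens the stress response and lowers heart rate should therefore leave this index higher during the stressor, and 1a predicts the reverse.

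The pilot exists to hand an effect size to a later, adequately powered trial, so the sign of that effect is part of what it delivers. Read against 1a as written, an RS arm that kept its HRV up while recalling discrimination would be reported as failing the hypothesis. An RS arm whose HRV fell would be reported as having lower cardiovascular risk.

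**Working it through.** No stated figure is at issue, so there is nothing to reproduce first. The check has two parts: a comparison of every statement that bears on HRV direction, and short arithmetic on what a reversed direction changes.

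**Statements side by side**

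| Place | Content | Implied favourable direction of vagally mediated HRV |
|---|---|---|
| Objectives, 1a | lower HRV listed as a health improvement | lower |
| Expected Findings | lowering HRV reduces cardiovascular risk | lower |
| Abstract, Background | RS goes with lower cardiovascular reactivity | higher under stress |
| Introduction, relational savoring section | RS lowers heart rate | higher |
| Primary Outcomes | index is vagally mediated | fixes the meaning: more vagal activity, higher value |
| Table 1 | HRV at the stressor, a level | none stated |
| Data Analytic Plan | ANCOVA, baseline HRV as covariate | none stated |

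The entries for the Abstract and the Introduction rest on one premise that the article does not spell out: vagal activity slows the heart, raises this index, and is withdrawn under stress. That is what the term vagally mediated denotes, and no outside figure is needed.

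**Could lower HRV mean a smaller HRV reaction?** Item 1a refers to HRV during the task, Table 1 names a level, and Expected Findings speaks of lowering HRV. None of these describes a change score. If the baseline covariate is resting HRV, a lower adjusted value during the stressor also means a larger drop from rest, which is more reactivity, not less.

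**What the reversal leaves alone.** Replacing the outcome y by −y in an ANCOVA changes the sign of the group coefficient and nothing else. In one simulated data set (40 per arm, one baseline covariate) the coefficient was 0.054 for y and −0.054 for −y, with p=0.751 both times. Two-sided power is likewise symmetric. At the article's d=0.24, with an assumed 40/40 split of the 80 participants and alpha 0.05, it is 18.8% for +0.24 and 18.8% for −0.24.

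**What it changes.** Inputs: d=0.24 from the Data Analytic Plan, used only as an illustrative size; 40 per arm, assumed; no covariate adjustment and no missing data, assumed.

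- Standard error of the standardised difference: √(2/40) = 0.2236.
- If the true effect is +0.24 towards higher HRV: 0.24/0.2236 = 1.073.
- Probability that the observed difference is positive: Φ(1.073) ≈ 0.86.

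So in about 86% of such trials the estimate would point towards higher HRV, and 1a would label that result as worse risk.

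**The case against.** The strongest reply is that the article is consistent about HRV itself. Objectives and Expected Findings agree, and no section says higher HRV is favourable. The conflict appears only once the physiological link is supplied. The Abstract does not define reactivity in terms of HRV, and the Introduction does not say that the lower heart rate was vagally driven or seen under stress. This stands as a limit: the article does not contradict itself in so many words. It does not remove the point, because the link follows from the index the article chose.

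A reader might also infer more than the article supports:

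- **That the outcome is scored with the wrong sign.** It is not. HRV is computed from interbeat intervals in the ordinary way. Only the expected direction is reversed, in one hypothesis and one Discussion sentence.
- **That power for a real benefit is lost.** That would require a one-sided test in the direction of 1a. The article states no sidedness, disclaims significance as its goal, and ties no decision rule to the sign.
- **That misreporting is certain.** The estimate will still show which arm had the higher HRV, so a careful author could read it correctly without reanalysis. The risk is misinterpretation, not damaged data.

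**Conclusion.** The point holds as an error of stated direction. Two sections name lower vagally mediated HRV as the benefit, nothing in the article corrects them, and the chosen index together with the article's own rationale points the other way. The repetition makes a single slip of the pen unlikely.

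Its reach is limited to interpretation. Estimate, two-sided p-value, power and sample size are the same whichever direction is written. It still matters, because the signed effect size is what the pilot is meant to supply and this is the only physiological component of the primary outcome.

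The conclusion rests on the ordinary meaning of vagally mediated HRV. The 86% figure depends also on the assumed equal split, complete data and d=0.24; the conclusion does not depend on that figure.

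**What to change.** Three wording changes:

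- In Objectives, 1a, give the favourable direction as *higher vagally mediated HRV* during the stressor task, keeping the reference to lower cardiometabolic risk.
- In Expected Findings, replace the reference to lowering HRV with *raising HRV*.
- In the analysis plan, before the groups are compared, state that a positive experimental-minus-waitlist difference in stressor-level HRV favours RS.

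The rewording should stay with stressor-level HRV, the quantity in Table 1. A smaller fall from rest is a different quantity: a participant can show a small fall with low HRV throughout, or a large fall with high HRV. It should not be added as though it were equivalent.

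The cost is wording only. Design, data collection, sample size and the ANCOVA are untouched, and if the model has already been fitted it need not be rerun.
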